### Survivor cohort

The survivor cohort consists of childhood cancer survivors who are three or more years from their last cycle of anthracycline therapy (recruitment target *n* = 920; actual recruitment *n* = 818). This cohort has been recruited from specialized survivor clinics at the six participating centres. A blood or saliva sample for DNA is collected at enrollment. Echocardiogram to assess function and blood sample for biomarkers are obtained at enrollment and annually over 2 years of follow-up (see Fig. 2 for timeline of sample and data acquisition in Survivor Cohort).

**Fig. 2 Fig2:**
[figure not shown]
Data and specimen acquisition from the Survivor Cohort. BIOMKR: Serum for biomarkers, ECHO: Echocardiogram, DNA: Blood for DNA, CMR: Cardiac Magnetic Resonance, CLIN: Gather baseline clinical data

Family and medical history, cancer therapy history and demographics are collected at baseline. Concomitant medications are collected at each study visit. All consented patients agree to provide a sample for genomics as well as serial echocardiograms at enrollment, and 12 and 24 months from baseline. Biomarker consent and consent for CMR are optional. Participants who consent to biomarkers provide 5-8 mL of blood at the time of each echocardiogram. Participants who consent to the CMR component of the study have a CMR at any one of the enrollment, 12 month or 24 month study time points (Table 3).

**Table 3 Tab3:** Schedule of Procedures/Evaluations in Survivor Cohort

Procedure/ Evaluation	Baseline (0 months)	Month 12 (± 8 weeks)	Month 24 (± 8 weeks)
Informed Consent/ Assent	X		
Demographics	X		
Cancer Therapy History	X		
Height (cm) & Weight (kg)	X	X	X
Medication and medical event review	X	X	X
Echocardiogram (ECHO)	X	X	X
Genetic Sample	Obtain one sample at any time point while patient is on-study		
OPTIONAL Biomarker Sample	X	X	X
OPTIONAL CMR	Occurs at one time only while patient is on-study.^a^		

^a^CMR will be performed in a subset of consented study patients only

### Data management

Demographic, treatment and outcome data is captured at each site and entered directly into a secure web-based application known as REDCap (Research Electronic Data Capture [34]). Patients have been assigned a unique subject number upon enrolment into the study. This is assigned at the site and registered in REDCap. Data entered into the REDCap database is de-identified at each recruiting centre through use of a unique study identifier. Study data entered into REDCap is verified by the coordinating centre at the Hospital for Sick Children and any inconsistencies or queries rre sent to the appropriate site coordinator for resolution in the REDCap database. REDCap maintains a built-in data verification feature as well as a built-in audit trail that logs all user activity and all pages viewed by every user (https://redcapexternal.research.sickkids.ca/). This will allow the coordinating centre to determine all the data entered, viewed or modified by any given user.

### Study outcomes

Based on paediatric and adult data that show that early cardiac remodelling precedes global dysfunction, the study will use remodeling parameters (left ventricular posterior wall thickness (LVPWT) Z-score and LV thickness to dimension ratio (TDR)) as markers of early cardiac injury that can identify patients who are at risk for progressive cardiac dysfunction later in life. Thus, the primary outcome measurement in each of the genomics, biomarker and imaging cores is the presence of one or more of the following at 12 months after anthracycline in the Acute Cohort, or at any study time point in the Survivor Cohort:Cardiac remodelling defined as an LVPWT or TDR z-score < −2.0 (or a reduction in LVPWT or TDR z-score by ≥1 standard deviation compared to baseline in the Acute group); orReduced LV EF (<55%) or a drop in LV EF of ≥10% over serial echocardiograms; orSymptomatic heart failure graded using New York Heart Association (NYHA) classification (or Ross heart failure class 2 in infants <2 years old).

This study is being conducted by three collaborative cores:

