**Fig. 1 Fig1:**
[figure not shown]
Data and specimen acquisition from the Acute Cohort. BIOMKR: Serum for biomarkers, ECHO: Echocardiogram, DNA: Blood or saliva for DNA, CLIN: Gather baseline clinical data

**Table 1 Tab1:** Inclusion and exclusion criteria by cohort

	Inclusion criteria	Exclusion criteria
Acute Cohort	1. Aged <18 years at time of cancer diagnosis; 2. Diagnosed with a new malignancy; 3. Cancer treatment plan will require therapy with ≥1 dose of an anthracycline chemotherapy 4. Pre-anthracycline; echocardiograms to occur at the recruiting site; 5. Normal cardiac function prior to the initiation of anthracycline therapy (LVEF >55%).	1. Patients with significant congenital heart defects; 2. Patients who were previously treated with anthracycline chemotherapy or radiation to the chest.
Survivor Cohort	1. Aged <18 years at time of cancer diagnosis; 2. Previously diagnosed with cancer and currently in remission; 3. Patients whose prior treatment plan included therapy with ≥1 dose of anthracycline chemotherapy; 4. Patients who completed their final dose of anthracycline ≥3 years ago; 5. Patients who completed their final dose of a chemotherapy agent other than anthracycline ≥1 year ago; 6. Routinely followed at the recruiting site approximately every 12 months.	1. Prior allogeneic stem cell transplant; 2. Patients with significant congenital heart defects; 3. CMR: general contraindications for a contrast enhanced CMR, and patients who require anaesthesia for MRI (typically <6 years of age) will be excluded.

Family and medical history and demographics are collected at baseline. Data on concomitant medications are collected at each study visit. A blood (4-6 ml) or saliva (2 ml) sample is collected for DNA extraction and genomic analysis. Serial 2D echocardiograms are obtained at baseline, and at 12 months post-final anthracycline therapy dose. Additional echocardiograms are obtained prior to each dose of anthracycline in consenting patients. A blood sample (5-8 ml per time point) is collected prior to each dose of anthracycline therapy, and at 3 months and 12 months post the last anthracycline dose. The consent for biomarker studies is optional. In a subset of patients over 6 years of age, patients are also approached for consent for a cardiac MRI at the 12 month follow-up time point (Table 2).

**Table 2 Tab2:** Schedule of procedures/evaluations in Acute Cohort

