#### Aim 1 (acute cohort)

The core will determine whether reduced myocardial strain measurements are observed after acute anthracycline exposure and whether these changes in strain parameters predict the occurrence of adverse cardiac remodeling (as measured by changes in LV dimension and wall thickness) or dysfunction (as measured by change in ejection fraction from baseline to 12 months after therapy).

A baseline echocardiogram will be completed prior to commencing cancer therapy using a standardized functional protocol (Additional file 1). The protocol will be repeated prior to each anthracycline administration (which varies depending on each patient’s cancer treatment protocol), and at 12 months after the last dose of anthracycline chemotherapy, as outlined in Fig. 1. All images will be sent electronically to the imaging core laboratory (The Hospital for Sick Children) for centralized analysis. To standardize image acquisition at the different sites, training of the individual sonographers was provided by the core laboratory. Based on M-mode and 2-D echocardiography, LVEF by biplane Simpson’s, LVPWT and LV TDR z-score will be measured and calculated as recommended by the paediatric quantification guidelines issued by the American Society of Echocardiography [35]. Speckle tracking echocardiography is used to measure strain measurements as described by Koopman et al. [36]. Mean circumferential strain will be calculated from the basal short axis views. Circumferential strain measurements obtained in 6 segments will be averaged. Mean longitudinal strain measurements will be obtained from the apical 4-chamber view. Mean values in 6 segments will be averaged. Secondary imaging parameters including diastolic function parameters, tissue Doppler measurements and other myocardial deformation measurements will also be obtained. These will be analyzed to evaluate their usefulness for the early detection of myocardial dysfunction.

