### Developing a risk prediction model

To achieve the primary objective of the Acute Cohort study (identifying patients at increased risk for therapy-induced cardiac disease prior to starting or during therapy), evolution of echocardiographic parameters over the treatment duration will be modeled in linear and non-linear regression models adjusted for repeated measures through a compound symmetry covariance structure. The resulting general estimating equations (GEE) will provide an estimate of the effect of anthracyclines over time for the entire cohort and the parameter estimate (slope of change over time) for each individual patient will be used as a potential predictor of therapy-induced cardiac damage. Twelve months after their final cycle of anthracycline chemotherapy, patients will be classified as having cardiac disease or not based on evidence of remodeling or decreased EF or CHF. Potential factors associated with acute cardiac change or cardiac damage at 12 months after treatment will be sought from patient demographics (e.g. age at treatment, gender), treatment (e.g. cumulative anthracycline dose, radiation exposure), genomics, serial biomarkers and echocardiographic measurements at baseline and during follow-up. Because of the very large number of potentially associated factors (and the multiple variations in format/time points for many factors), we will have to reduce the number of candidate factors using a pre-specified algorithm. As exploratory analyses, univariate regression models using therapy-induced cardiac changes or cardiac disease at 1 year (present vs. absent) as the dependent variable, and all other collected variables as potential independent variables will be created. This will allow exploration of variables potentially associated with therapy-induced cardiac damage including assessment of collinearity, ill condition (variables with no events in one of the study groups) or amount of missing data. All variables with univariable *p*-value <0.30, excluding collinear variables, ill conditioned variables or variables with an unacceptable amount of missing data will be included in a bootstrap bagging algorithm. A total of 5000 random sub-samples will be created and for each of those, a mixed stepwise regression model will be used to obtain multivariable predictors for therapy-induced cardiac damage. The proportion of sub-samples in which a given variable is selected is called reliability. Variables with high reliability (>50%) will then be included in a multivariable regression model with backward selection of variables to obtain a final model. This algorithm significantly improves the accuracy of variable selection, reduces the probability of sampling bias and corrects for multiple comparisons better than a post-hoc analysis would. At the end of this algorithm we will be left with a limited number of associated factors, all with high reliability. Based on the reliability estimates, we will be able to determine whether the risk of therapy-induced cardiac changes or cardiac damage at 1 year after anthracycline exposure is driven by baseline measurements (including clinical, genomic, echocardiographic or biomarkers), by reaching specific milestones during anthracycline treatment, by change over time in cardiac dimension/function and biomarkers during anthracycline treatment, or by a combination of all three.

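### In the Acute Cohort, the same baseline echo values help define the remodelling event and are screened as its predictors, so a baseline echo risk factor can be an artefact whose direction depends on unstated repeatability

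*Protocol article*

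**What the plan says.** **Outcome.** Under Study outcomes, the remodelling limb has two routes in the Acute Cohort. One is absolute: "Cardiac remodelling defined as an LVPWT or TDR z-score < −2.0". The other is a change: "a reduction in LVPWT or TDR z-score by ≥1 standard deviation compared to baseline in the Acute group". Remodelling, an EF criterion and symptomatic heart failure together form the primary outcome of all three cores.

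**Measurements.** There is one baseline study and one outcome study: "Serial 2D echocardiograms are obtained at baseline, and at 12 months post-final anthracycline therapy dose". Imaging Core Aim 1 (acute cohort) confirms the single pre-treatment study: "A baseline echocardiogram will be completed prior to commencing cancer therapy using a standardized functional protocol". No confirmatory echo, repeatability limit or baseline adjustment is attached to the change route.

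**Eligibility.** Table 1 requires "Normal cardiac function prior to the initiation of anthracycline therapy (LVEF >55" per cent). It sets no requirement on baseline LVPWT or TDR.

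**Predictors.** Developing a risk prediction model draws candidates from "genomics, serial biomarkers and echocardiographic measurements at baseline and during follow-up", and the univariable screen covers the cardiac outcome against "all other collected variables as potential independent variables will be created". The stated exclusions are for collinearity, ill-conditioning and missing data. None removes a variable that is itself part of the outcome definition. The section ends by planning to decide whether risk comes from baseline values (echocardiographic ones included), from milestones or change during treatment, or from a combination.

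**The concern.** A raw change is the follow-up value minus the baseline value, so any chance error in the baseline value enters the event with its sign reversed. A child whose baseline LVPWT happened to read high is more likely to show a 1-SD fall with no injury at all. On the change route this makes a high baseline look like a risk factor.

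The absolute route couples baseline and outcome in the opposite direction. A child who was below −2 before treatment, and who is eligible because only LVEF is checked, is likely to be below −2 again at 12 months. That child is then counted as an anthracycline case, so a low baseline looks like a risk factor.

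At stake is a planned headline conclusion, namely whether baseline echo measurements drive risk, and the content of the risk algorithm meant to inform care. Either artefact could enter the final model as a reliable predictor.

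**Working it through.** The article states no event rate, power or echo repeatability, so there is no figure of its own to reproduce. The check asks what the stated rules do in children with no true change.

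**Inputs from the article:** change cut of 1 SD (read as 1 z unit); absolute cut z < −2.0; either LVPWT or TDR suffices; one baseline and one 12-month echo; 307 recruited (target 270); screen at p < 0.30.

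**Assumed, because not given:** no true change; z-scores with SD 1 at both visits; LVPWT–TDR correlation 0.6; test–retest ICC from 0.6 to 0.9.

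**One parameter, change route.** The difference between two readings has variance 2(1 − ICC), so P(fall ≥ 1) = Φ(−1/√(2(1 − ICC))). At ICC 0.7: √0.6 = 0.775, −1/0.775 = −1.29, and Φ = 9.8%. The correlation of baseline with change is −√((1 − ICC)/2), which is −0.39 at ICC 0.7.

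**Both parameters and both routes**, by simulation of 400,000 children per ICC:

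| ICC | Fall, one parameter | Fall, either | Remodelling event (fall or z < −2) | Of 307, if all unharmed | AUC of baseline LVPWT for that event |
|---|---|---|---|---|---|
| 0.9 | 1.3% | 2.2% | 6.0% | 18 | 0.28 |
| 0.8 | 5.7% | 9.6% | 12.6% | 39 | 0.51 |
| 0.7 | 9.8% | 15.8% | 18.1% | 56 | 0.59 |
| 0.6 | 13.2% | 20.8% | 22.6% | 69 | 0.64 |

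**Why the direction changes.** With LVPWT–TDR correlation varied from 0 to 0.7, the odds ratio per SD of baseline LVPWT was:

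| ICC | Change route alone | Full remodelling event |
|---|---|---|
| 0.9 | 1.3–1.7 | 0.35–0.54 |
| 0.8 | 1.4–1.8 | 0.92–0.99 |
| 0.7 | 1.5–1.9 | 1.2–1.3 |

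At ICC 0.9 about 63% of the null events come from the absolute route alone. Of the 12-month LVPWT values below −2, about 59%, 43%, 32% and 24% were already below −2 at baseline (ICC 0.9 to 0.6).

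**Near cancellation is not absence.** At ICC 0.8 and correlation 0.5, the null event rate across four baseline bands (below −1, −1 to 0, 0 to 1, above 1) is 19.2%, 9.1%, 11.8% and 18.2%. This U shape gives almost no linear slope.

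**Effect on the p < 0.30 screen**, at n = 270: baseline LVPWT passes in 61–73% of samples at ICC 0.7, 39–46% at 0.8 and 84–96% at 0.9, against 30% by chance. At 0.9 it passes in the low-baseline direction.

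**Check of remedies.** Judging change on the 12-month value given baseline brings the spurious odds ratio to 0.99–1.01 for ICC 0.5 to 0.9. Counting z < −2 only when it is new lowers the null event rate at ICC 0.7 only from 18.1% to 17.0%. It also removes the offsetting route, so the high-baseline AUC rises from 0.59 to 0.63 at ICC 0.7 and from 0.51 to 0.57 at ICC 0.8.

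**The case against.** The strongest reply has four parts.

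- **Size is unknown.** It rests entirely on repeatability that the article does not give. Images are read centrally, the protocol is standardized and sonographers were trained. At ICC 0.9 a false fall in a given parameter occurs in only about 1% of children. This stands, and it is why a range is shown. Better reading shrinks the error but does not break the coupling, and at high ICC the pre-existing low values take over.
- **The outcome is broader.** EF and heart-failure events also count and would dilute the artefact. This stands; they were not modelled.
- **Detail may lie in the analysis plan.** Covariate handling often does. But the outcome rule, the candidate pool, the exclusions and the planned conclusion are all stated here, and together they produce the problem.
- **A repaired model still has false cases.** This is correct and is carried into the fix.

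Three stronger readings are tempting but unsupported. A reader might infer that high baseline wall thickness is bound to be selected as a risk factor. That follows for the change route taken alone, but the documents define the event as a fall or z < −2, and for that event the signal cancels near ICC 0.8 and reverses at 0.9. Nor was the bagging step with its 50% reliability cut simulated.

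A reader might also infer that every genomic, biomarker and strain association is biased toward the null. The change route applies only to the Acute group, not to the 818 survivors. Bias toward the null also requires error independent of the predictor, which fails for baseline echo values.

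Finally, one might speak of regression to the mean in the cohort as a whole. Children are not selected on LVPWT or TDR, so the mean need not shift. The false cases come from variation around a single baseline reading.

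**Conclusion.** The point holds for the Acute Cohort's remodelling limb and the risk model built on it. The stated rules place baseline measurement error and pre-existing low values in both outcome and predictors, and the plan intends to interpret the resulting association. With no true change, SD 1 and LVPWT–TDR correlation 0.6, the null event rate is about 6% to 23% over ICC 0.9 to 0.6, and the AUC of baseline LVPWT runs from about 0.28 to 0.64.

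The sign of any baseline echo risk factor therefore cannot be interpreted without knowing repeatability. The counts out of 307 assume that every child is unharmed and has both echoes, so they illustrate scale and are not forecasts. The size in the full composite, with EF and heart failure included, is not established.

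**What to change.** 1. In the Acute models, take baseline LVPWT z, TDR z and EF out of the candidate pool and force them in as adjustment terms. Allow for curvature, since a linear term misses the U shape near ICC 0.8. Do not interpret them as discovered risk factors, and report the AUC gain of other predictors over baseline alone.
2. Alongside the composite, analyse 12-month LVPWT and TDR z-scores as continuous outcomes adjusted for their baseline values.
3. As a sensitivity analysis, count z < −2 in the Acute Cohort only if it was absent at baseline, and always together with step 1. Used alone, this rule enlarges the high-baseline artefact at ICC of about 0.8 or below.
4. Report the core laboratory's repeatability for LVPWT and TDR, and acknowledge that the binary composite still contains false cases from the change route.

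**Cost.** Steps 1 to 3 are changes of analysis wording using measurements already scheduled. They bring slightly more analysis and slightly fewer events in step 3. They do not appreciably lower the number of false cases in the binary outcome, which is why step 4 is needed.

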### CORE 1: Genomics

The Genomics Core will perform a comprehensive genome-wide search to identify genes associated with anthracycline cardiotoxicity.

The study will use a nested case-control approach. Patients who are anthracycline sensitive (i.e. develop cardiac dysfunction despite low anthracycline doses), and those who are anthracycline resistant (i.e. have preserved cardiac function despite high anthracycline doses) will be included in a discovery cohort. These patients will undergo whole exome sequencing to identify genes associated with cardiotoxicity. Genes in pathways related to anthracycline absorption, distribution, metabolism, and excretion, and genes important in cardiac response to injury will be prioritized in the analysis. Non-genetic risk predictors will be included in the regression model. The top-ranked genes that are enriched for variants and are deemed biologically relevant will undergo targeted sequencing in the remainder of the cohort which will serve as a replication cohort.

### CORE 2: Biomarkers

The Biomarker Core will explore whether existing and novel biomarkers allow for more accurate diagnosis of acute and late treatment-related cardiac toxicity.

#### Aim 1 (acute cohort)

To determine and validate which of the currently available dynamic protein biomarkers detectable in serum during the acute phase of anthracycline administration can predict early cardiac remodeling.

A panel of biomarkers that have been shown to indicate cardiac stress or injury, including N-terminal pro b-type natriuretic peptide (NTproBNP), high sensitivity troponin (hsTnT), myeloperoxidase (MPO), and insulin-like growth factor binding protein 7 (IGF-BP7) will be evaluated. The discovery cohort will be derived from the children enrolled in the Acute Cohort at The Hospital for Sick Children. The validation cohort will be derived from similarly recruited patients in the Acute Cohort from London, Ottawa and Hamilton. Patients will have serum collected at the time points specified in Fig. 1. The serial serum samples will be assayed for levels of the target markers at each of the collection time points. Both the individual marker levels and the patterns of change over time will be evaluated against the primary outcome (evidence of remodeling, decreased EF or CHF at 1 year). The candidate biomarkers will be evaluated using quality controlled assays on the most appropriate platforms (e.g. for NTproBNP, hsTnT and IGF-BP7, the Roche Elecsys platform available in the Biomarker Core laboratory will be used, and for MPO, standard human serum ELISA kits such as that provided by Eagle Bioscience, NH will be used). These will be performed in replicate with appropriate controls. The best candidates from the discovery cohort will then be applied to the validation cohort to determine the reproducibility and cross population validity of the marker performance.

